## Abstract

**Introduction:**

Angiography with indocyanine green (ICG) fluorescence performed before thyroidectomy would allow identification of the vascularization of parathyroid glands, maximizing efforts for preserving functioning glands intraoperatively. The rationale of the study was based on the hypothesis that showing the vascular pattern of the parathyroid glands by means of ICG angiography before performing the thyroidectomy could prevent permanent hypoparathyroidism.

**Methods and analysis:**

We propose a randomized single-blind controlled and multicenter clinical trial to assess the efficacy and safety of ICG angiography-guided thyroidectomy to identify the vascular pattern of the parathyroid glands versus conventional thyroidectomy in patients scheduled for elective total thyroidectomy. Patients will be randomized 1:1 to ICG angiography-guided thyroidectomy (experimental group) or conventional thyroidectomy (control group). Patients in the experimental group will undergo ICG angiography before thyroidectomy to identify the feeding vessels of the parathyroid glands and then, post-thyroidectomy ICG angiography to predict immediate parathyroid gland function by scoring the degree of fluorescence of the glands. Patients in the control group will undergo post-thyroidectomy ICG angiography only. The primary outcome measure will be the rate of patients with permanent hypoparathyroidism. Secondary outcome measures will be rate of postoperative hypoparathyroidism, the percentage of well vascularized parathyroid glands remaining in situ, the levels of iPTH and serum calcium after surgery and the influence of the type of vascular pattern of the parathyroid glands over these outcomes, as well as the safety profile of ICG angiography.

**Discussion:**

The results will contribute to adopt a new surgical strategy based on intraoperative ICG angiography before performing total thyroidectomy, according to which the rate of permanent hypoparathyroidism could be substantially reduced.

**Clinical trial registration:**

ClinicalTrials.gov. identifier NCT05573828.

## Introduction

1

Permanent hypoparathyroidism as a sequela of thyroid gland surgery continues to be a real and challenging clinical problem. Parathyroid failure may occur after surgical procedures to treat both benign and malignant thyroid disorders usually as a result of trauma, devascularization, parathyroid autotransplantation, or inadvertent resection of the glands (1). Most people with permanent hypoparathyroidism have to take calcium and vitamin D supplements for life, with long-term consequences affecting the quality of life and increasing economic costs (2, 3). The reported rate of permanent hypoparathyroidism is highly variable between less than 4% and up to 15% depending on the different definition of hypoparathyroidism used in each study and especially to the different time cutoff applied to distinguish transient from permanent hypoparathyroidism (4–6).

Novel fluorescence techniques have been developed for improving intraoperative identification of the parathyroid glands and to avoid postoperative hypocalcemia. Indocyanine green (ICG) angiography has been shown to be a valuable technique for identifying and assessing the perfusion of the parathyroid glands during total thyroidectomy (7, 8). Quantitative scoring systems based on a black and white scale depending on the amount of ICG flowing through the gland and categorized as 0, black (nonvascularized), 1, gray/heterogeneous (partially vascularized), and 2, white (well vascularized) have been successfully used for predicting early postoperative hypocalcemia after total thyroidectomy (9, 10). Moreover, a single-gland ICG score of 2 in any parathyroid gland after completion of thyroid surgery is a reliable method in prediction of early post-thyroidectomy hypocalcemia (11, 12). Recently, Benmiloud et al. (13) have shown the feasibility of using intraoperative ICG mapping angiograms of the parathyroid glands to improve vascular preservation during thyroid surgery. In an assessment of 76 parathyroid glands, those glands with informative angiography (visible vascular pattern) showed a higher percentage of ICG score of 2 than for parathyroid glands with uninformative angiography (13).

In a previous study of our group, a comparison of immediate and permanent hypocalcemia was made in two cohorts of patients who underwent total thyroidectomy and ICG-angiography (14). In patients included in the prospective cohort (n = 36), ICG-angiography was performed after identification of the parathyroid glands to show their vascular supply prior to surgical removal of the thyroid gland (angiography-guided thyroidectomy), whereas in the historical comparative cohort (n = 84), ICG-angiography was performed only at the end of the surgery. The rates of early and permanent hypocalcemia were significantly lower in the angiography-guided thyroidectomy group (5.6% *vs.* 26.2%, *p* = 0.011, and 0% *vs.* 11.9%, *p* =0.032, respectively) than in controls. Moreover, a significant higher rate of well vascularized parathyroids at the end of the surgery (score 2) in the angiography-guided thyroidectomy group (52.9% vs. 39.2%, *p* = 0.018) was also seen (14). Results obtained in this cohort study provided the rationale for the design of a randomized controlled clinical trial. The hypothesis is that showing the vascular map of the parathyroid glands before performing the thyroidectomy by means of ICG angiography could prevent the development of postoperative hypoparathyroidism. Therefore, we here describe the protocol of a randomized, single-blind, controlled, and multicenter study to assess the efficacy and safety of ICG angiography-guided thyroidectomy versus conventional thyroidectomy in patients undergoing total thyroidectomy.

## Materials and methods

2

### Research design

2.1

This study is a randomized, single-blind, controlled, parallel arm, and multicenter trial. In this single-blind design only the patient is blind to the allocation. Recruitment starts in October 2022 and ends in December 2024. Participants will be randomly (1:1) divided into ICG angiography-guided thyroidectomy (experimental group) that included an ICG-angiography before thyroidectomy to identify the vascular pattern of the thyroid glands, and conventional thyroidectomy (control group). Post-thyroidectomy ICG to predict parathyroid function by scoring the degree of fluorescence of the glands will be performed in all patients. The study is registered in the ClinicalTrials.gov (NCT05573828) and will follow the guidelines of Consolidated Standards for Reporting Trials (CONSORT) (15). Flow chart is shown in **Figure 1**.

**Figure 1 f1:**
[figure not shown]
Flow chart of the GuiArte trial.

### Research setting

2.2

This study will recruit 394 eligible subjects from the Units of Endocrine Surgery of tertiary care hospitals in Spain. The University Hospital of Bellvitge in Barcelona (Spain) will be the reference center. Inclusion and exclusion criteria are shown in **Table 1**.

**Table 1 T1:** Inclusion and exclusion criteria.

**1.- Inclusion Criteria** (1) Patients ≥ 18 years of age with a surgical indication for elective total thyroidectomy with or without central cervical lymph node dissection due to thyroid pathology. (2) The patient has the capacity to understand the study and agrees to participate in it, signing the corresponding informed consent document.
**2.- Exclusion Criteria** (1) Previous surgical intervention on the thyroid or parathyroid gland. (2) Associated hyperparathyroidism that requires associating a parathyroidectomy in the same surgical act. (3) Patients with contraindications for the administration of ICG except for patients with clinical hyperthyroidism, autonomous thyroid adenomas, and focal and diffuse changes of the thyroid gland who will undergo total thyroidectomy. (4) Current drug use or alcohol abuse that could interfere with compliance with the study requirements. (5) Participation in any other drug trials in the month prior to randomization.

### Randomization and blinding

2.3

After baseline assessment, the study will use a 1:1 ratio to randomly divide the subjects into 2 groups. Randomization will be performed using a computer-generated table of random numbers. The group assignment will be performed by an independent statistician who would be blinded to the recruitment, intervention, and evaluation of participants. Blinding of researchers (who perform the surgical procedures) to group assignment would not be possible to the specific nature of the study. The principal investigator at each participating center will be aware of the randomization arm before entering the operating room. However, statisticians who will perform the statistical analysis after the follow-up of patients will be blinded to group assignment. At the same time, the study is single-blind randomized trial. In this study, all participants will be unaware of the allocation to the experimental or the control group.

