### Postoperative care and follow-up

2.5

During hospitalization, the clinical course of patients will be controlled to assess the presence of hypoparathyroidism, complications, or adverse events (16). Intact parathyroid hormone (iPTH) levels will be measured at 24 hours postoperatively (i.e. the morning after surgery) according to the technique used at each hospital laboratory. Corrected serum calcium levels will be measured 24 hours after surgery. Clinical practice guidelines of each center will be followed for postoperative administration of calcium and vitamin D. Those patients with postoperative hypoparathyroidism will be followed clinically in association with periodical measurements of iPTH, corrected serum calcium, and vitamin D levels at 1, 3, 6, and 12 months after surgery or until hypoparathyroidism resolution.

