Study variables will be collected by the researchers through clinical visits and results of laboratory analyses. Data will be stored in a codified electronic database specifically designed for the purpose of the study. Monitorization of study data will be performed by external personnel unaware of details of the study. To examine the benefits of identifying the vascular pattern of the parathyroid glands using an ICG angiography before thyroidectomy for preventing permanent hypoparathyroidism, a full analysis set will be performed, that is, all patients randomized who will be operated on, and followed postoperatively until permanent hypoparathyroidism will be resolved or for a maximum of 12 months after surgery. Categorical variables will be expressed as frequencies and percentages, and continuous variables as mean ± standard deviation or median and interquartile range (IQR) (25th-75th percentile). The Shapiro-Wilks test will be used to assess the normal distribution of data and the Levene’s test to assess homoscedasticity. Categorical variables will be analyzed with the chi-square test or the Fisher’s exact test, and quantitative variables with the Student’s *t* test or the Mann-Whitney *U* test according to conditions of application. The risk ratio (RR) and the 95% confidence interval (95%) will be calculated to assess the probability of permanent hypoparathyroidism. Univariate and multivariate logistic regression models adjusted by confounding variables will be performed to identify risk factors for permanent hypoparathyroidism. *P* < 0.05 is set as the significance level. The Statistical Package for the Social Sciences (SPSS) version 26 for Windows will be used for data analysis.

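### 24-hour iPTH is measured with each hospital's own assay but compared between arms in a pooled test that ignores centre

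*Protocol article*

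**What the plan says.** The trial is multicentre: "This study will recruit 394 eligible subjects from the Units of Endocrine Surgery of tertiary care hospitals in Spain". The number of centres is not given. Table 1 admits patients for "elective total thyroidectomy with or without central cervical lymph node dissection".

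Under Postoperative care and follow-up (2.5), two things are left to the centre:

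- iPTH the morning after surgery is measured "according to the technique used at each hospital laboratory".
- "Clinical practice guidelines of each center will be followed for postoperative administration of calcium and vitamin D".

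Under Definitions (2.6), permanent hypoparathyroidism is a need for calcium and/or vitamin D at 12 months, either to keep calcium normal or to prevent symptoms. Early hypoparathyroidism can also be met by supplements given before the calcium measurement. Secondary outcome 3 (2.7.2) compares iPTH levels at 24 hours between the arms.

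Under Sample size and statistical analysis (2.8), "Categorical variables will be analyzed with the chi-square test or the" Fisher exact test, quantitative variables get a t or Mann-Whitney test, and a risk ratio with confidence interval is given for the primary outcome. None of these is described as stratified or adjusted. The one adjusted analysis is a logistic model looking for risk factors for permanent hypoparathyroidism. Its covariates are not named, and it does not cover iPTH.

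On allocation, Randomization and blinding (2.3) says that "the study will use a 1:1 ratio to randomly divide the subjects into 2 groups" and then: "Randomization will be performed using a computer-generated table of random numbers". Strata and blocks are neither mentioned nor excluded.

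**The concern.** The plan allows a known source of between-centre variation and then names tests that leave it in the error term. If laboratories use techniques that read at different levels, raw iPTH values from different hospitals are not on one scale. A pooled t or Mann-Whitney test treats the gap between two assays as if it were variation between patients.

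At stake is precision for a secondary outcome that bears directly on the proposed mechanism. A real difference in iPTH could be estimated with a wider interval than the data allow. The same reasoning applies in principle to the hypoparathyroidism rates, because local prescribing can influence who meets the definitions, so its size there has to be checked as well.

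**Working it through.** **Inputs from the article (2.8).** 2% versus 8%, alpha 5%, power 80%, loss about 5%, 197 per arm, 394 in total.

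**Assumed, because the article gives no figure.** The share of iPTH variance due to centre and, for the primary outcome, the number of centres, the share with neck dissection, and the size of centre and dissection effects.

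**1. The plan's own figure.** With the two-sided arcsine formula, h = 2·asin(√0.08) − 2·asin(√0.02) = 0.2897 and n = 2·((1.960 + 0.842)/h)² = 187.0. Then 187.0/0.95 = 196.9, which rounds to 197 per arm. The stated size is reproduced. It is an unadjusted calculation with no allowance for centre.

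**2. iPTH.** Let ρ be the share of total variance due to centre. The pooled test works with the total variance, and a centre-adjusted one with the within-centre share 1 − ρ. The ratio of standard errors is therefore √(1 − ρ), ignoring the small cost of estimating the centre terms. If r is the between-centre SD divided by the within-centre SD, ρ = r²/(1 + r²).

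| ρ (assumed) | r | SE factor √(1 − ρ) | Information kept by the pooled test |
|---|---|---|---|
| 5% | 0.23 | 0.975 | 95% |
| 10% | 0.33 | 0.949 | 90% |
| 20% | 0.50 | 0.894 | 80% |
| 30% | 0.65 | 0.837 | 70% |

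For example, r = 0.5 gives ρ = 0.25/1.25 = 0.20. The pooled comparison then has the precision of an adjusted one on about 0.80 × 394 = 315 patients.

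**3. Primary outcome.** The simulation assumed 374 evaluable patients, 10 equal centres, 30% with dissection and marginal rates of 8% and 2%, with 4,000 replicates per cell (Monte Carlo error about 0.7 points). The Cochran-Mantel-Haenszel (CMH) test used centre crossed with dissection, that is 20 strata. Stratified lists used blocks of 4. Power in %:

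| Centre SD (logit), dissection odds ratio | Unstratified list: chi-square / CMH | Stratified list: chi-square / CMH |
|---|---|---|
| 0, 1 | 79.0 / 77.4 | 80.1 / 79.5 |
| 0.5, 2 | 78.6 / 76.4 | 78.9 / 79.1 |
| 0.8, 3 | 78.9 / 77.5 | 77.5 / 78.6 |
| 1.2, 4 | 77.9 / 77.9 | 77.0 / 79.4 |

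- Stratifying both list and test, against neither: 79.0 to 79.5, 78.6 to 79.1, 78.9 to 78.6 and 77.9 to 79.4. The gain is about 0 to 1.5 points.
- Changing the test alone: about −2.3 to +0.1 points if the list is unstratified, and about −0.7 to +2.4 if it is stratified.
- Type I error of chi-square with an unstratified list: 4.6% to 5.0%. With a stratified list it drops to 3.6% to 3.7% in the two stronger scenarios, so the unadjusted test is then conservative.

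**4. Events.** 187 × 0.08 + 187 × 0.02 = 18.7. With 197 per arm, 19.7. So 19 to 20 events must be spread over all strata.

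**The case against.** The strongest reply has four parts.

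- **Allocation.** A reader might infer that randomisation is simple, so that arms may be unbalanced within centres. The documents do not support this. A blocked or stratified list is also computer-generated, and a condensed article commonly leaves such detail to the full protocol. This objection stands, and nothing here rests on simple randomisation. Advice to adopt permuted blocks does not follow either. The article does not rule blocks out, blocks within centre would make later allocations partly predictable to surgeons who know the arm, and recruitment is planned to end in December 2024.
- **Validity.** A reader might infer that chance imbalance invalidates the comparison. It does not: type I error stays at its nominal level and the confidence interval already allows for imbalance. Even with an unstratified list, the share with dissection would differ between arms by more than 10 points with probability only 1.3% to 4.7% (dissection in 20% to 50% of patients, assumed). This stands too.
- **The primary outcome.** Local guidelines do not simply determine it. It is defined by need for treatment at 12 months, whereas those guidelines concern supplements after surgery. The link to early hypoparathyroidism is closer. A logistic model with adjustment is planned for the primary outcome, although for risk factors. The precision argument is weak here, as the simulation shows.
- **The analysis plan.** A plan that is not shown may refine the tests. That is possible, but the article does more than stay silent: it names the tests, and as named they ignore centre.

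What is left untouched is iPTH: local assays, a pooled test, and no adjusted analysis of that outcome.

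**Conclusion.** The point holds for iPTH as a loss of precision, not as bias or inflated error. Accounting for centre would reduce the standard error by 2.5% to 16% if centre explains 5% to 30% of the variance. That range is an assumption; if the hospitals' techniques agree closely, the gain lies at or below its lower end.

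For the primary outcome the unadjusted test is valid and little is to be gained. Stratifying by many small cells can even cost a little power when the list is not stratified. The one condition that would change this is a stratified list, since an unadjusted test would then be somewhat conservative.

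**What to change.** **iPTH.** In the analysis section, replace the pooled test for 24-hour iPTH with one of two analyses, chosen before unblinding:

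- a van Elteren rank test stratified by centre; or
- a linear model for log iPTH with arm and centre as factors.

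Scaling to each laboratory's reference limit is optional. With one limit per centre, scaling changes neither the within-centre ranks nor the arm effect in the log-scale model. It helps where small centres are pooled or a hospital changes its technique during the trial. The rank test is the safer choice if values fall below a detection limit.

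**Primary outcome (optional).** Report a Mantel-Haenszel risk ratio and risk difference stratified by centre, with small centres pooled by a rule fixed before unblinding. Keep the strata few: with 19 to 20 expected events, many would otherwise hold no event and add nothing to the risk ratio.

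**Link to allocation.** State how the list was made. If the full protocol shows that it was stratified, use those strata in the analysis.

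**Cost.** Analysis wording only, with centre recorded for each patient. There is no change to treatment, assays or sample size. The iPTH model spends a few degrees of freedom on centre.

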### Intervention

2.4

All patients will be managed similarly in the preoperative period. Supplementation with vitamin D will be recommended for patients with 25-OH vitamin D deficit (< 20 ng/mL). None of the patients will receive preoperative calcium supplementation. The protocol for standard thyroidectomy includes starting with luxation of each thyroid lobe and performing careful dissection to minimize damage to the parathyroid glands, followed by search and visual identification of the glands in each lobe, as well as in orthotopic localizations.

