#### ICG angiography-guided thyroidectomy

2.4.1

All the participant surgeons will conduct a formative meeting with the leading group to homogenize the procedures and the definitions. The procedure will include performing an ICG angiography of the parathyroid glands before removal of the thyroid gland. To this purpose, after the luxation of the thyroid lobe and the identification of the parathyroid glands, 1 mL of the contrast material will be administered through a peripheral vein after dilution of a powdered vial of 25 mg (Verdye^®^, Diagnostic Green GmbH, Aschheim-Dornach, Germany) of ICG in 10 mL of sterile water. After a few seconds, ICG-enhanced fluorescence imaging of the vascular pattern of the parathyroid glands previously identified will be acquired using a near-infrared camera. Visualization of the vascular pattern of the parathyroids will include identification of a clear feeding vessel with its pedicle (defined pattern) or a vascular network around the parathyroid gland without a clear feeding vessel (non-defined pattern). After identification of the vascular map of each parathyroid gland, the dissection will be performed in a guided manner to minimize its damage. The surgical procedure will continue with total removal of the thyroid lobe and then performing an ICG angiography of the parathyroids after injection of 3 mL of the contrast material, and obtaining a black and white near-infrared view. The fluorescence of the glands (back and white imaging) will be assessed intraoperatively by the operating surgeon, and the degree of fluorescence will be classified according to the color of the gland reflecting the degree of perfusion. The color of the gland can vary from black (suggesting that it is not vascularized and likely non-viable), to white (suggesting that it is well vascularized and viable). Glands will be classified as 0, black (nonvascularized); 1, gray/heterogeneous (partially vascularized); and 2, white (well vascularized). Both autotransplanted and parathyroid glands identified in the histopathological report are devascularized and will be scored as 0. The procedure will be the same in the other lobe, but the initial doses will be 3 mL. During the dissection, repeated doses to reevaluate the vascularization are allowed when needed until a maximum of 5 mg/kg. In patients undergoing central neck dissection, ICG angiography to assess the degree of parathyroid glands vascularization will be performed after each procedure, lymphadenectomy and thyroidectomy.

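### The arm is disclosed before theatre, earlier than the procedure needs; opening it just before the first ICG injection would protect entry to the analysis set and the first-lobe dissection

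*Protocol article*

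**What the plan says.** All references are to the protocol article.

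- **Time of randomisation (2.3):** "After baseline assessment, the study will use a 1:1 ratio to randomly divide the subjects into 2 groups".
- **Time of disclosure (2.3):** "The principal investigator at each participating center will be aware of the randomization arm before entering the operating room".
- **Reason given (2.3):** "Blinding of researchers (who perform the surgical procedures) to group assignment would not be possible to the specific nature of the study". No separate reason is given for disclosure before the operation begins.
- **Shared first steps (2.4):** standard thyroidectomy starts with luxation and careful dissection, "followed by search and visual identification of the glands in each lobe". The control arm also identifies the glands by eye (2.4.2).
- **First arm-specific step (2.4.1):** "after the luxation of the thyroid lobe and the identification of the parathyroid glands, 1 mL of the contrast material will be administered".
- **ICG in both arms (2.1):** "Post-thyroidectomy ICG to predict parathyroid function by scoring the degree of fluorescence of the glands will be performed in all patients".
- **Analysis set (2.8):** randomised patients who undergo surgery and are then followed for up to 12 months. A randomised patient who is never operated on is outside it.
- **Eligibility (2.2, Table 1):** patients "with a surgical indication for elective total thyroidectomy with or without central cervical lymph node dissection due to thyroid pathology"; one exclusion is "Associated hyperparathyroidism that requires associating a parathyroidectomy in the same surgical act".

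**The concern.** That surgeons cannot be blinded explains why they must know the arm during the guided part of the operation. It does not explain why they must know it before the operation starts. Two routes for bias stay open without need.

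1. **Entry to the analysis.** Between disclosure and incision a patient can be cancelled or postponed. If that depends on the arm, even unintentionally, the two analysed groups are no longer the randomised groups, because section 2.8 leaves out patients who are not operated on.
2. **First-lobe dissection and search.** Luxation, early dissection and the search for glands come before the injection but are done with the arm known. They bear on gland trauma and devascularisation, which the Introduction lists as causes of parathyroid failure. They also determine how many glands can be scored for the secondary outcome on well-vascularised glands, and the operating surgeon does that scoring.

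Only the patient is blind during the trial (2.1), so the time at which the arm is opened is one of the few safeguards the design can still use.

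**Working it through.** **Step 1. Where the arms diverge.**

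| Step | Experimental | Control | Arm needed? |
|---|---|---|---|
| Luxation of first lobe, early dissection (2.4) | yes | yes | no |
| Visual identification of its glands (2.4, 2.4.1, 2.4.2) | yes | yes | no |
| ICG injection before lobe removal (2.4.1) | yes | no | **yes, first time** |
| ICG after removal (2.1) | yes | yes | no |

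The arm is first needed at the third row. ICG and the camera must be on hand in every case because of the fourth.

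**Step 2. The plan's sample size, and whether the fix changes it.** Inputs from 2.8: 2% against 8%, alpha 5% (taken as two-sided), power 80%, loss about 5%. Arcsine formula: h = 2·asin(√0.08) − 2·asin(√0.02); n = 2(1.960 + 0.842)²/h² = 188 per arm; 188/0.95 = 198. The plan states 197, so the figure reproduces to within one patient. None of these inputs depends on when the arm is opened, so 197 per arm (394) stands.

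**Step 3. How few events carry the result.** Evaluable per arm: 197 × 0.95 ≈ 187. Expected events: 187 × 0.08 = 14.96 in the control arm and 187 × 0.02 = 3.74 in the experimental arm. With 15 control events and 187 per arm:

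| Experimental events | Fisher p | Chi-square p |
|---|---|---|
| 5 | 0.036 | 0.022 |
| 6 | 0.070 | 0.043 |
| 7 | 0.12 | 0.079 |

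One event decides either test: the sixth for Fisher, the seventh for chi-square.

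**Step 4. Illustration of route 1 (assumptions, not in the document).** There is no true effect and the rate is 8% in both arms. A share s of patients is high risk with event risk r_h; the others have r_l = (0.08 − s·r_h)/(1 − s). A fraction q of the high-risk patients leaves the experimental arm only. Its rate becomes p_E = [s(1−q)r_h + (1−s)r_l]/(1 − s·q), with 187(1 − s·q) patients left.

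Example: s = 0.30, r_h = 0.16, so r_l = (0.08 − 0.048)/0.70 = 0.0457. With q = 0.10, p_E = (0.0432 + 0.032)/0.97 = 7.75%.

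The last column is the chance of a significant result favouring the experimental arm (normal approximation, two-sided 5%), which is 2.5% without selection. Ranges cover s = 0.30 with r_h = 0.16 and s = 0.20 with r_h = 0.20.

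| q | Patients leaving | p_E | False-positive rate |
|---|---|---|---|
| 10% | 4 to 6 | 7.8% | about 3.1% |
| 25% | 9 to 14 | 7.4% | 4.1 to 4.2% |
| 50% | 19 to 28 | 6.6 to 6.7% | 6.9 to 7.1% |

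For scale, the planned loss is 0.05 × 197 ≈ 10 patients per arm. The last row would need about two to three times that number, all of them high-risk and all from one arm.

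**Step 5. Route 2** cannot be sized from the document, which gives no figures on first-lobe dissection or gland search.

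**The case against.** The strongest reply is that nothing here is a contradiction or a wrong figure. The article says openly that operators are unblinded. It standardises procedures through a meeting of the surgeons and blinds both the patients and the analysing statisticians. When to open the arm is a design preference. The sentence also names the centre's principal investigator, who need not be the operating surgeon, and it does not say how long before surgery the arm is known. Opening it in theatre needs a working system at every centre. All of this is fair, and it keeps the point to an inexpensive improvement. It does not supply a reason for early disclosure, and the sentence on blinding makes clear that operators do know the arm.

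Two stronger readings are tempting, and the document does not support them.

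- **A reader might infer that eligibility is settled in theatre.** Table 1 asks for an indication for total thyroidectomy, and excludes associated hyperparathyroidism that needs parathyroidectomy. Both read as preoperative, and randomisation follows baseline assessment. No rule in 2.8 drops an operated patient because of an intraoperative finding or a changed extent of surgery. Selection can therefore act through patients not operated on or not followed, but not through exclusions made during the operation.
- **A reader might infer that central neck dissection will differ by arm to some stated degree.** The article calls dissection optional. It does not say when the decision is taken, how often it occurs or what risk it carries. Any size put on such an imbalance would come from outside the document.

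It is also true that later opening protects only part of the operation. The lobes are done in sequence, so the arm is known for the second lobe and for anything decided after the first injection.

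**Conclusion.** The point holds in limited form. The arm is disclosed earlier than the described procedure requires, and no reason for that timing is stated. Opening it just before the first possible injection would close the route through patients never operated on, since allocation and surgery would then coincide. It would also blind the first-lobe luxation, early dissection and gland search. It would not address loss to follow-up after surgery, which the analysis set also leaves out.

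The expected size is modest and its direction unknown. On the assumed risks in the illustration, small selection by arm barely moves the false-positive rate (2.5% to about 3.1%), and it must be large to matter much. The case for change rests on the low cost of the remedy and on a result that one event can decide, not on any demonstrated bias.

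**What to change.** Replace the disclosure sentence in 2.3 with wording to this effect:

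1. Eligibility and the planned extent of surgery, including whether central neck dissection is intended, are recorded before allocation.
2. The allocation is opened in the operating room after luxation of the first lobe and visual identification of its glands, immediately before the first possible ICG injection.
3. Patients cancelled before that point are not randomised and do not count towards the 394.
4. Every patient whose allocation is opened is analysed as allocated; 2.8 should be aligned with this.

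**Cost:** a wording change, a sealed or web allocation usable in theatre at each centre, and a brief pause in the operation. No extra patients, staff or procedures are needed, and ICG and the camera are already required in both arms.

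**Limit:** for the second lobe and later decisions on extent, the recorded plan prevents nothing. It only makes departures by arm visible, so they should be tabulated by arm.
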